## Abstract

**Background:**

Bipolar disorders (BD) are among the most severe mental disorders with first clinical signs and symptoms frequently appearing in adolescence and early adulthood. The long latency in clinical diagnosis (and subsequent adequate treatment) adversely affects the course of disease, effectiveness of interventions and health-related quality of life, and increases the economic burden of BD. Despite uncertainties about risk constellations and symptomatology in the early stages of potentially developing BD, many adolescents and young adults seek help, and most of them suffer substantially from symptoms already leading to impairments in psychosocial functioning in school, training, at work and in their social relationships. We aimed to identify subjects at risk of developing BD and investigate the efficacy and safety of early specific cognitive-behavioural psychotherapy (CBT) in this subpopulation.

**Methods/Design:**

EarlyCBT is a randomised controlled multi-centre clinical trial to evaluate the efficacy and safety of early specific CBT, including stress management and problem solving strategies, with elements of mindfulness-based therapy (MBT) versus unstructured group meetings for 14 weeks each and follow-up until week 78. Participants are recruited at seven university hospitals throughout Germany, which provide in- and outpatient care (including early recognition centres) for psychiatric patients. Subjects at high risk must be 15 to 30 years old and meet the combination of specified affective symptomatology, reduction of psychosocial functioning, and family history for (schizo)affective disorders. Primary efficacy endpoints are differences in psychosocial functioning and defined affective symptomatology at 14 weeks between groups. Secondary endpoints include the above mentioned endpoints at 7, 24, 52 and 78 weeks and the change within groups compared to baseline; perception of, reaction to and coping with stress; and conversion to full BD.

**Discussion:**

To our knowledge, this is the first study to evaluate early specific CBT in subjects at high risk for BD. Structured diagnostic interviews are used to map the risk status and development of disease. With our study, the level of evidence for the treatment of those young patients will be significantly raised.

**Trial registration:**

WHO International Clinical Trials Platform (ICTRP), identifier: DRKS00000444, date of registration: 16 June 2010.

## Background

Bipolar disorders (BD) are among the most severe mental disorders. Lifetime prevalence estimates range from 1 to 5% [1-5]. They are associated with a recurrent or chronic course, insufficient clinical response, and psychosocial impairment in a substantial number of patients. First clinical signs and symptoms frequently appear in adolescence and early adulthood (median age at disease onset 17.5 years) [6-8]. Usually there is, however, a long lag before the correct diagnosis is established and treatment is often delayed for many years [6,7,9-13]. Delayed treatment and an increasing number of illness episodes have been associated with a decreased probability of response to treatment [14] and an adverse course of illness [15,16]. The combination of long undetected illness with no or inadequate treatment and significant psychosocial impairment renders early identification and intervention a vital role in disease management.

To date, there has been relatively little research into early identification and intervention in subjects at risk for BD. First at-risk criteria based on clinical presentation and/or family history have been proposed and pilot evaluation data are available [17,18]. Moreover, structured diagnostic instruments for the prospective identification of at-risk constellations for BD have been developed and are currently validated [19,20]. These structured measures are applied in the present study. Regarding treatment in these at-risk states, in a recent systematic review [21] we identified three studies: an exploratory, controlled study of multi-family psycho-educational psychotherapy from the group of Fristad and colleagues [22], an open, uncontrolled easibility study of family-focussed therapy by Miklowitz *et al*. [23] and the subsequent randomised controlled study of the same group [24]. Treatment with the studied interventions (in addition to treatment as usual, including psychopharmacology) showed a potential for symptom reduction and prevention of conversion to BD and a significantly faster recovery from initial mood symptoms and more time in remission during follow-up compared to control conditions. The results, however, have to be interpreted with caution, because of the small sample sizes, permission of medication treatments in the intervention and control groups in all studies, and the lack of a control group or data on conversion in one study. Until now, there is no data on the efficacy of early cognitive-behavioural psychotherapy (CBT) in high-risk subjects for BD. In current clinical routine, neither screening for at-risk states nor specialised diagnostic processes are implemented, and even in cases that present with significant affective symptoms, no specific intervention is routinely offered before the full disorder manifests.

### Objectives/hypotheses

CBT has been shown to be effective in BD (see [25,26]). Previous research suggested that, although there was no significant difference in overall recurrence rates, CBT is more effective than treatment as usual in bipolar patients with few, as compared to those with many, episodes in their history [27]. We therefore hypothesise that the intervention might be more effective in the early stages of disease and even more so in the prodromal phase.

We therefore aimed to conduct a prospective randomised controlled trial to compare an experimental intervention (early specific CBT including stress management and problem solving strategies with elements of mindfulness-based therapy (MBT) in a group setting) against unstructured group meetings. We hypothesised that subjects randomly allocated to the experimental intervention show less psychosocial impairment and specified affective symptomatology at 14 weeks compared to subjects receiving the control intervention.

## Methods/Design

### Design of the study

This is a randomised controlled multi-centre clinical trial to evaluate the efficacy and safety of a specific CBT for young people at-risk for BD versus unstructured group meetings for 14 weeks each with long-term follow-up until week 78. Figure 1 summarises the trial flow. Study subjects, outcome assessors, and the statistician are blinded to treatment allocation. The study is conducted according to good clinical practice (GCP) standards and has been approved by the responsible local ethical committees.

**Figure 1 F1:**
[figure not shown]
**Trial flow.** Legend: CBT (cognitive-behavioural psychotherapy), FU (follow-up).

### Description of intervention and control condition

In the absence of a published manual, an intervention was specifically designed to meet the needs of the bipolar high-risk clientele (*BEsT (be)for(e) Bipolar*, © [name], [name] and [name] 2010). It consists of specific CBT, including stress management and problem solving strategies with elements of MBT in a group setting. The newly developed intervention was based on the manual ‘Cognitive psychoeducational therapy for bipolar disorders’ by Schaub *et al*. [28]; modules for stress management and problem solving strategies from the manual ‘Kognitiv-verhaltenstherapeutisches Behandlungsmanual’ by Meyer and Hautzinger [29] were integrated. Additionally, mindfulness exercises from MBT [30] are used. The aforementioned manuals were chosen by means of aptitude for the purpose of the intervention and availability of validation data. Modules were adapted to the needs of at-risk subjects similarly to the approach described by Bechdolf and Juckel [31] as some modules conceptualised for patients with full manifestation were weakened and terms of probability/risk were emphasised. Treatment modules of *BEsT (be)for(e) Bipolar*© include psycho-education about mental illnesses, and BD in particular, including treatment options, handling of early warning signs and crisis planning for prophylaxis, structuring of activities, cognitive strategies, and sensitisation for a balanced life rhythm. The control condition consists of unstructured group meetings where therapists are instructed to avoid therapeutic measures in any way possible. Both interventions are applied in groups of four to five subjects and in the same frequency and duration with 14 sessions each of 90 minutes within 14 weeks (one per week). To increase transparency and documentation as well as for analysis and comparability, sessions are videotaped.

### Setting and participants

Study participants were initially recruited at five, now at seven participating university centres which provide in- and outpatient care for patients with unipolar depressive and bipolar disorders (Department of Psychiatry and Psychotherapy, University Hospital Carl Gustav Carus Dresden; Department of Psychiatry, Ruhr University Hospital Bochum; Department of Psychiatry and Psychotherapy, University Medical Center Hamburg-Eppendorf; Department of Child and Adolescent Psychiatry and Psychotherapy, LWL University Hospital Hamm; Department of Psychiatry, University Hospital Cologne; Department of Psychiatry and Psychotherapy, University Hospital Würzburg, Department of Psychiatry, Psychosomatics and Psychotherapy, Charité-University Medicine, CCM; all Germany). Most of them additionally run early recognition centres for psychoses and/or affective disorders.

Key inclusion criteria for subjects include:

• Positive family history for affective and/or schizoaffective disorders (first and/or second degree relative)

• Reduction in psychosocial functioning/coping with demands of daily living (measured by the Social Interview Schedule, SIS, [32], German version: [33]) in the last 12 months compared to the previous 12 months

• Specified affective symptomatology (sub-threshold mania and/or at least sub-threshold depression with cyclothymic features and/or cyclothymic features, definitions see below) (measured by the Early Phase Inventory for bipolar disorders (EPI*bipolar*, ©[name] and [name] 2010, [19]) and the Bipolar Prodrome Symptom Scale (BPSS)-Prospective (©[name] 2007, [20]) in the last 12 months compared to the previous 12 months

• Aged 15 to 30 years

• Language capacity to take part in the trial

• Written informed consent to participate in the study.

Definitions of specified affective symptomatology are similar to those proposed by Bechdolf *et al*. [17]: sub-threshold mania is defined as a period of at least two consecutive days of abnormally and persistently elevated, expansive or irritable mood plus at least two of the following criteria: inflated self-esteem or grandiosity, decreased need for sleep, more talkative than usual or pressure to keep talking, flight of ideas or subjective experience that thoughts are racing, distractibility, increased goal-directed activity or psychomotor agitation. At least sub-threshold depression is defined as depressed mood or loss of interest or pleasure plus at least two of the following criteria: fatigue or loss of energy, feelings of worthlessness or excessive or inappropriate guilt, insomnia or hypersomnia nearly every day, psychomotor retardation or agitation, diminished ability to think or concentrate, recurrent thoughts of death/recurrent suicidal ideation or significant weight loss over a period of at least one week. Cyclothymic features are defined as numerous episodes with sub-threshold manic symptoms not meeting the definition of sub-threshold mania and numerous episodes with depressive symptoms.

Key exclusion criteria include:

• A history of treated or untreated manic episode of at least four days duration (Structured Clinical Interview for *Diagnostic and Statistical Manual of Mental Disorders, 4th edition* (DSM-IV) Disorders, SCID, in German: [34])

• A history of treated or untreated psychosis of at least seven days duration (SCID)

• Main symptomatology must not be present solely within the context of personality disorder or cyclothymia (SCID)

• Organic brain disorder

• Acute suicidality

• Severe, unstable medical condition (for example, cancer, neurological diseases)

• Intake of psychotropic medication (only medication for sleep disturbances and a stable antidepressant medication with serotonin reuptake inhibitors (SSRIs), venlafaxine, duloxetine, mirtazapine or valdoxan (stable means intake for at least eight weeks) are allowed, all other drug doses must be tapered-down and stopped before randomisation).

Rationale for choosing the presented inclusion and exclusion criteria are as follows. First degree relatives of affected individuals have a ten-fold increased risk to also develop the disease compared to relatives of unaffected controls [35]. Twin and adoption studies have provided compelling evidence for heritable factors playing a major role in the pathogenesis of BD (see [36]). A genetically enriched population with first affective symptoms that already impact psychosocial functioning seemed to us the best way to identify subjects at high risk for developing BD. Participants must not already be diagnosed as having unipolar or bipolar affective disorders but can be diagnosed as having cyclothymia, attention deficit/hyperactivity disorder (ADHD), personality disorder or psychosis of less than seven days duration, if the symptomatology is not explained solely by this diagnosis. In view of the often unspecific presentation of high-risk subjects, this ensures reduction of false-negative recruitment, while at the same time of course the risk for false-positive enrolment is increased. The pilot findings by Bechdolf *et al*. [17,18] which indicated conversion rates to four days of mania in up to 30% within 12 months, depending on the criteria applied, support this approach of inclusion criteria definition. The diagnostic procedure comprises using the SCID plus the result of a consensus board of two clinical psychiatrists per centre.

Subjects in both treatment groups are allowed to use unstructured consultations with their usual treating physician at any time. After the intervention period, subjects in both groups are allowed to use unstructured psychotherapy sessions and psychopharmacotherapy if needed (restricted to intermittent symptomatic treatment of unspecific symptoms such as sleep disturbances and anxiety/agitation administered no longer than seven days). As mentioned, a stable antidepressant medication with SSRI, venlafaxine, duloxetine, mirtazapine or valdoxan (stable means intake for at least eight weeks) is allowed at randomisation and can be prolonged during the study. Formal, structured psychotherapy and psychopharmacotherapy other than described before results in study drop-out.

As mentioned in the inclusion criteria, written informed consent is obtained from each subject after thorough information about the study has been provided.

### Outcome measures

Primary efficacy endpoints:

• Psychosocial functioning/coping with demands of daily living (SIS) at 14 weeks

• Specified affective symptomatology (Hamilton Rating Scale for Depression (HAMD, [37]), Young Mania Rating Scale (YMRS, [38]), EPI*bipolar*, BPSS) at 14 weeks

Key secondary endpoints:

• SIS at 7, 24, 52 and 78 weeks

• Mini version of the International Classification of Functioning, Disability and Health for Mental Disorders (MINI-ICF-P, [39,40]) at 7, 14, 24, 52 and 78 weeks

• Specified affective symptomatology (HAMD, YMRS, EPI*bipolar*, BPSS) at 7, 24, 52 and 78 weeks

• Perception of, reaction to and coping with stress: Alltags-Belastungs-Fragebogen (ABF, [41]), Trierer Inventar zum chronischen Stress (TICS, [42]), Stress-Reaktivitäts-Skala (SRS, [43]), Fragebogen zum Umgang mit Belastungen im Verlauf (UBV, [44]), Fragebogen zur Erfassung von Ressourcen und Selbstmanagementfähigkeiten (FERUS, [45]) at 7, 14, 24, 52 and 78 weeks

• Development of bipolar disorders at 52 and 78 weeks (SCID).

Assessment of safety: structured assessment of adverse events (GCP standard, interview: description of type, severity and relation to intervention). See Table 1 for an overview of instruments applied.

**Table 1 T1:** Instruments applied at individual study visits

** Time**	**Baseline**	**FU 1**	**FU 2**	**FU 3**	**FU 4**	**FU 5**
**Instruments**	**Wk -1**	**Wk 7**	**Wk 14**	**Wk 24**	**Wk 52**	**Wk 78**
SIS	X	X	X	X	X	X
MINI-ICF-P	X	X	X	X	X	X
HAMD	X	X	X	X	X	X
YMRS	X	X	X	X	X	X
EPI*bipolar*	X	X	X	X	X	X
BPSS	X	X	X	X	X	X
ABF	X	X	X	X	X	X
TICS	X	X	X	X	X	X
SRS	X	X	X	X	X	X
UBV	X	X	X	X	X	X
FERUS	X	X	X	X	X	X
SCID	X				X	X

Legend: FU, follow-up; Wk, week; SIS, Social Interview Schedule, English version: [32], German version: [33]); MINI-ICF-P, Mini version of the International Classification of Functioning, Disability and Health for Mental Disorders, [39,40]; HAMD, Hamilton Depression Symptom Scale 17 item version, [37]; YMRS, Young Mania Rating Scale, [38]; EPI*bipolar*, Early Phase Inventory for bipolar disorders, ©[name] and [name] 2010, [19]; BPSS, Bipolar Prodrome Symptom Scale-Prospective, ©[name] 2007, [20]; ABF, Alltags-Belastungs-Fragebogen, [41]; TICS, Trierer Inventar zum chronischen Stress, [42]; SRS, Stress-Reaktivitäts-Skala, [43]; UBV, Fragebogen zum Umgang mit Belastungen im Verlauf, [44]; FERUS, Fragebogen zur Erfassung von Ressourcen und Selbstmanagementfähigkeiten, [45]; SCID, Structured Clinical Interview for DSM-IV Disorders, in German: [34]. The baseline time is week minus 1.

Rationale for choosing the presented outcome measures are as follows. We chose coping with demands of daily living as one primary outcome measure as it is a sensitive measure of changes in psychosocial functioning that in turn highly influences the long-term outcome of the disorder. Our study population consists of subjects at high risk for developing BD; they do not fulfill the diagnosis (yet) but already show impairment of psychosocial functioning. Improving this should have a great impact on the course of the disease development either by postponing/alleviating or even preventing the full-blown disorder. Additionally, we use the change in affective symptomatology as a primary endpoint since psychosocial functioning is only in part explained by psychiatric symptomatology.

To get an idea about adherence on the therapist’s part to the treatment manual or instructions regarding the control group setting, videotaped treatment sessions which have been developed based on the German adapted version of the Cognitive Therapy Scale for Psychosis [46] by Wittorf *et al*. [47], will be reviewed. Adherence on the subject’s part is assessed by checking on participation in the sessions as well as home work completion in the active intervention groups.

### Blinding and methods against bias

An independent statistician uses a centrally computer-generated block-designed randomisation procedure stratified by centre. Only the principal investigator of the study (AP) and the psychotherapist of the individual centre are notified of the randomisation result; subjects and outcome assessors are kept blinded. The statistician who will later analyse the study results is kept blinded throughout the whole study.

An intensive three days training of GCP, study procedures and applied instruments was provided to psychotherapists and raters before onset of the study to minimise differences between centres. Regular trainings are provided throughout the study. All group sessions (in the intervention and control groups) are videotaped and stored for analysis. The trial is managed with help of the departmental clinical trial centre.

To ensure the performance according to the study protocol and the quality of the study monitoring is performed in each study centre at appointed time intervals and as needed (at least per centre once at initiation of the study, once after the first subject was randomised, once after 1/3, 2/3 and 3/3 of subjects were recruited, and once when the last subject completed the study), the monitoring process is performed according to prepared standard operating procedures (SOPs). The monitor checks completeness and plausibility of the data and aligns the study data to the original data (Source Data Verification). This is accomplished by accessing the original subjects’ charts; the subjects will give their permission to that procedure within the informed consent form. The monitor ensures the basic claim of integrity and protection of the subjects’ privacy. If not all data are examined, the monitor must justify that procedure and must pull a proper random sample for the check.

Supervision of the trial is present in the form of a scientific advisory board including members especially experienced in assuring data quality and safety. They also supervised the development of the application protocol and the progress of the trial including decision making on whether to perform interim analyses or modify/stop the trial in cases of unforeseen problems arising.

### Power

Sample size for the ANCOVA will be approximated with the two-sided unpaired *t*-test. The primary outcome measure is the difference in the adapted overall social maladjustment score. Here, the number of items in the categories M and S with a rating of 2, 3 or 4 is divided by the number of applicable items in the categories M and S. With an estimated effect size of about 0.5, a sample size of 2 times 50 patients is required to show this difference with a power of 80% and an alpha of 5% (calculated with G*Power 3.1.2).

We assume that the compliance will be relatively good here since the intervention does not result in major side effects and the subjects already experience symptoms. However, we assume conservatively that there will be about a 30% drop-out rate, an estimate that was accounted for in the sample size estimation. Follow-up of subjects that drop out of the study will last for the planned duration of the study.

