### Relevance of study for clinical practice and future research

Our approach to identify patients with a positive family history in potentially early stages of BD is comparable to that in high-risk subjects for psychosis. In the present study, clinical presentation, impairment of psychosocial functioning, and family history is combined to define persons at risk of a significant conversion risk.

Studies show that cognitive-behavioural psychotherapy (CBT) is effective in patients with BD in reducing symptomatology. Scott *et al*. [27] showed that although there was no significant difference in overall recurrence rates, CBT was more effective than treatment as usual in patients with few compared to those with many recurrent bipolar episodes in their history. We therefore suggest that the intervention might be more effective in the early stages of disease and so even more in the prodromal phase. In persons at risk for psychosis, CBT was shown to be effective in alleviating symptomatology. The transition risk was reduced as long as the intervention (psychopharmacological and psychotherapeutic) could reduce the symptomatology. After the end of the intervention however, general transition rates increased and then almost equalled that of the group without intervention; see [49-53]. There were however, as stated above, enduring effects of CBT in that the likelihood of being prescribed antipsychotics in the three-year follow-up was reduced ([50]). Interestingly, in the group of subjects with psychological vulnerabilities targeted by the intervention, the transition risk to psychosis was also significantly reduced [49,50]. In full-blown schizophrenia, of course, CBT without psychopharmacology would be not effective enough [54].

Additionally, we suggest that the components of the studied intervention tackle symptomatology associated with the factors that influence components of the vulnerability-stress-system (for example, sleep regulation, stress management and handling of personality features) and, therefore, should be best suited to alleviate/postpone or even prevent onset/conversion to BD. Most importantly, evidence of the effectiveness and adverse events of CBT in subjects at high risk for BD is missing so that our study will answer this clinically relevant question regardless of the study results.

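### The Power section's own inputs (two-sided t-test, d = 0.5, alpha 5%) give about 70% power with 2 x 50, not 80%, and its drop-out sentence does not fit that number

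*Protocol article*

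**What the plan says.** All of the sample size reasoning stands in the Power section of the protocol article.

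- Method: "Sample size for the ANCOVA will be approximated with the two-sided unpaired" t-test.
- Outcome: "The primary outcome measure is the difference in the adapted overall social maladjustment score", which is the SIS endpoint.
- Effect: "With an estimated effect size of about 0.5".
- Result: "a sample size of 2 times 50 patients is required to show this difference with a power of 80% and an alpha of 5" per cent, calculated in G*Power 3.1.2.
- Drop-out: the authors assume "about a 30% drop-out rate, an estimate that was accounted for in the sample size estimation".

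The Statistical analysis section makes the primary analysis an ANCOVA of week-14 SIS on group, baseline SIS, affective symptomatology, centre, age, sex and education. It is by intention to treat, with LOCF for missing values. No section states a one-sided test, a correlation between covariates and outcome, or a second sample size inflated for drop-out.

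**The concern.** Everything needed to check the number is given in one paragraph, so the check does not depend on an unseen analysis plan or full protocol. The usual figure for d = 0.5, two-sided 5% and 80% power is in the sixties per group, so 50 looks too small.

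This is the only power statement in the article, and it concerns a primary endpoint. Someone interpreting a non-significant SIS result would lean on the 80%. If the declared test has only about 70%, that reader would take a null result as stronger evidence against an effect of the assumed size than the stated calculation allows. The drop-out sentence adds to the problem: a calculation that already uses all 50 per group to reach its target has no room left for a 30% loss.

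**Working it through.** **Inputs, all from the Power section:** unpaired t-test, two-sided, alpha 0.05, d = 0.5, n = 50 per group, target power 0.80, drop-out 0.30.

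**Formula.** For n per group, df = 2n − 2 and the noncentrality is λ = d·√(n/2). Two-sided power is P(|T| > t(0.975, df)), where T is noncentral t with df and λ. One-sided power uses t(0.95, df) and the upper tail only.

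**1. The stated figure, as stated.** n = 50: df = 98, λ = 0.5·√25 = 2.50, critical value 1.984. Power = **69.7%** (70.5% by the normal approximation). This does not reproduce the stated 80%.

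**2. The n that the stated inputs require.**

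| n per group | λ | two-sided power |
|---|---|---|
| 50 | 2.50 | 69.7% |
| 63 | 2.81 | 79.5% |
| 64 | 2.83 | 80.1% |

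So 64 per group (128 in total) are needed: 14 more per group, 28 more in all.

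**3. What does come close to 50.** One-sided 5%, n = 50: critical value 1.661, power = 79.9%. Strictly, 51 per group are needed to pass 80% (80.6%); the normal approximation gives 50.

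**4. Slack in the effect size.** With 50 per group, two-sided:

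- d = 0.45: 60.6%
- d = 0.55: 77.7%
- d = 0.566: 80%

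**5. What the ANCOVA could add.** Suppose d = 0.5 is on the unadjusted SD, and the covariates together have multiple correlation R with week-14 SIS. The effective effect size is then d/√(1 − R²), ignoring the few degrees of freedom spent on covariates. Reaching 80% at n = 50 requires 0.5/√(1 − R²) = 0.566, so R = √(1 − (0.5/0.566)²) ≈ **0.47**. The article gives no R. Over an assumed range:

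| R (assumed) | power at 50 per group |
|---|---|
| 0.30 | 73.7% |
| 0.47 | 80.1% |
| 0.50 | 81.6% |
| 0.60 | 87.2% |

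**6. Drop-out.** If 50 per group are randomised and 30% give no data, 50 × 0.7 = 35 remain. Then λ = 0.5·√17.5 = 2.09, critical value 1.995, two-sided power = **54.1%** (66.5% one-sided), and the effect detectable with 80% power is d = 0.68. Conversely, 64 evaluable per group with 30% loss would mean 64/0.7 = 91.4, so 92 randomised per group (184 in total).

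**The case against.** The strongest reply is that the t-test only approximates the ANCOVA. Adjustment for baseline SIS and the other covariates usually gains precision, and step 5 shows that a moderate multiple correlation would bring 50 per group to 80%. This stands in part. A reader might infer from the 69.7% that the planned analysis has a 30% false-negative rate; the document does not show that, because 69.7% belongs to the t-test approximation. It does not rescue the stated figure either. The section attaches 80% to the plain t-test and assumes no correlation.

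A second reply is that an effect of *about* 0.5 leaves room. It does not leave enough: d = 0.55 still falls short, and rounding could equally run downwards.

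A third concerns the cause. It is tempting to say that the calculation was run one-sided. The near match at 79.9% makes this plausible, but 51 rather than 50 is the exact one-sided answer, and d = 0.57 would also give 50. The text says two-sided and no section says otherwise, so the cause remains an inference.

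A fourth is that drop-out may already be handled. If 50 were the evaluable number, about 50/0.7 = 71.4, so 72 per group, would be randomised; if ITT with LOCF analysed all of them, two-sided power would be about 85%. But no such number is stated: the section calls 2 x 50 the patients required and then says drop-out was included. LOCF can keep drop-outs in the analysis, which is why 54% is the lower end and not the expected value.

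Finally, a reader might set this against the Discussion's statement that "our study will answer this clinically relevant question regardless of the study results". That sentence is about missing evidence on effectiveness and adverse events and makes no power claim, so the point should not rest on it.

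**Conclusion.** Wrong as written. Under the inputs that the Power section declares, 2 x 50 has 69.7% power and not 80%, and 80% needs 64 per group. The shortfall is about 10 percentage points of power, or 28 patients in total. It is too large for rounding or for the choice between normal and t calculations.

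This conclusion rests only on the article's own test, effect size, alpha and n, with all 50 per group analysed. If the 50 include a 30% loss and drop-outs give no data, the t-test figure is about 54%.

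The power of the planned ANCOVA remains unknown: it reaches 80% with 50 analysed per group only under an assumed multiple correlation of about 0.47 or more. What is established is a false power statement for the declared test and an unreconciled drop-out sentence, not a particular error rate for the primary analysis.

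**What to change.** Restate the Power section along these lines:

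*With data from 50 subjects per group, the two-sided 5% t-test has about 70% power for d = 0.5 and 80% power for d = 0.57. If d = 0.5 refers to the unadjusted SD, the ANCOVA reaches 80% only if the covariates together correlate with week-14 SIS at about 0.47 or more (an assumption).*

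Keep the test two-sided; switching to one-sided to match the number would alter the type I error control that the text declares.

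In the same section, say whether 2 x 50 counts subjects before or after the 30% drop-out, and correct the sentence that says drop-out was allowed for. If 50 per group are randomised, give both ends: about 70% when all 50 are analysed, and about 54% (detectable d = 0.68) when only 35 give data. If a larger number is to be randomised, state it.

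The cost is wording. No extra patients are needed, and the stated power becomes less favourable.

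### The 30% drop-out said to be built into the sample size is not visible in the only figure given, 2 × 50, and the stated two-sided test falls short of 80% power even with no loss

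*Protocol article*

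**What the plan says.** All of the sizing is in the Power section of the protocol article.

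- Method: "Sample size for the ANCOVA will be approximated with the two-sided unpaired *t*-test".
- Outcome: "The primary outcome measure is the difference in the adapted overall social maladjustment score", that is, a score from the Social Interview Schedule (SIS).
- Inputs and result: "With an estimated effect size of about 0.5", "a sample size of 2 times 50 patients is required", "with a power of 80% and an alpha of 5% (calculated with G*Power 3.1.2").
- Drop-out, in the next paragraph: "we assume conservatively that there will be about a 30% drop-out rate, an estimate that was accounted for in the sample size estimation".

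The same paragraph adds that subjects who drop out continue to be followed for as long as planned. The Statistical analysis section specifies an intention-to-treat ANCOVA at week 14, adjusted for baseline values among other covariates, with missing values filled by last observation carried forward (LOCF).

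No other section gives a total. Trial status reports only that half had been randomised by March 2013, and the monitoring schedule under Blinding and methods against bias is set in thirds of recruitment.

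**The concern.** The drop-out sentence is a positive statement about how the number was obtained, so it can be tested against the number. The only number is presented as the direct result of a t-test calculation. The section shows no inflation step and does not give an evaluable number and a number to randomise separately.

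Readers are told that the trial keeps 80% power on a primary endpoint after 30% attrition. If it does not, a non-significant result could be taken as adequately powered evidence of no effect.

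**Working it through.** **Inputs from the Power section.** Two-sample t-test, two-sided, alpha 0.05, power 0.80, effect size d = 0.5, 50 per group, drop-out 30%. The section does not say whether 50 is randomised or analysed, or at which time point the 30% applies.

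**Formulas.** Power comes from the noncentral t distribution with 2n − 2 degrees of freedom and noncentrality d × √(n/2). The normal approximation to the sample size is n = 2(z_α + z_β)²/d² per group. Inflation for drop-out is n/(1 − 0.30).

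**Step 1: reproduce the plan's figure.**
- Two-sided, normal approximation: 2 × (1.960 + 0.842)²/0.25 = 62.8, so 63. The exact t-test gives 63.8, so 64 per group.
- One-sided, normal approximation: 2 × (1.645 + 0.842)²/0.25 = 49.5, so 50. The exact t-test gives 50.15, with 79.9% power at 50.

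The printed 50 is therefore not reproduced by the stated two-sided test. It matches an uninflated one-sided 5% test.

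**Step 2: power at the printed size with no loss.** n = 50, noncentrality 0.5 × √25 = 2.5: two-sided power is 69.7%.

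**Step 3: suppose 50 per group already includes the 30%.** The base is 50 × 0.70 = 35 per group, noncentrality 0.5 × √17.5 = 2.09.

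| n = 35 per group | Power at d = 0.5 | d needed for 80% |
|---|---|---|
| Two-sided 5% | 54.1% | 0.68 |
| One-sided 5% | 66.5% | 0.60 |

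Neither test gives 80% at an effect size of about 0.5, so 50 cannot be a base number inflated for 30% loss.

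**Step 4: suppose 50 per group is the analysable number.** The number to randomise is 50/0.70 = 71.4, so 72 per group (144 in total). The article does not state this number. The stated two-sided inputs would lead to 64/0.70 = 91.4, so 92 per group (184 in total).

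**Step 5: split the shortfall when 35 per group are observed.** From 80% to 69.7% is about 10 points, due to the two-sided test. From 69.7% to 54.1% is about 16 points, due to drop-out. The total is about 26 points.

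**Step 6: sensitivity to covariate adjustment.** This needs a baseline-outcome correlation ρ, which the article does not give. The values below are assumptions. The effective effect size is 0.5/√(1 − ρ²).

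| Assumed ρ | Power, 50 per group | Power, 35 per group |
|---|---|---|
| 0 | 69.7% | 54.1% |
| 0.3 | 73.7% | 58.0% |
| 0.5 | 81.6% | 66.3% |
| 0.7 | 93.4% | 82.3% |

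**The case against.** **Drop-out is not the same as a missing week-14 value.** Drop-outs stay in follow-up, and under Setting and participants a subject becomes a drop-out by starting formal psychotherapy or non-permitted medication, so may still be assessed. The 30% might also refer to week 78 and not week 14. Everyone is analysed, with LOCF for gaps. This stands. A reader might infer that the trial has 54% power; the documents do not support that as an unconditional statement. But if all 100 contribute, the drop-out rate played no part in the size, and the two-sided figure is still only 69.7%.

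**The effect size of 0.5 may already be reduced for attrition.** That is a recognised way to allow for drop-out, and the article does not rule it out. So it would be too strong to say that no reading could make the sentence true. But the article does not say it, and it would still leave 69.7% two-sided power at 50 per group.

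**The ANCOVA gains power from baseline covariates.** It may, as step 6 shows. The Power section, however, chooses the t-test as its approximation, claims no such gain and states no correlation. With 35 per group, the correlation would have to be near 0.7 to restore 80%.

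**LOCF might push power lower still.** A reader might infer this by assuming that drop-outs gain nothing: d = 0.7 × 0.5 = 0.35, with 41% power at 50 per group. The documents do not support that figure. Table 1 schedules the SIS at week 7, so a value obtained during treatment can be carried forward. The article also does not say whether 0.5 is a full-adherence effect, so the reduction could count attrition twice.

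**Conclusion.** The statement that 30% drop-out was accounted for cannot be traced to the only sample size given. At d = 0.5, 2 × 50 matches an uninflated one-sided test; the stated two-sided test gives 69.7% with complete data.

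The size of the further loss depends on what 2 × 50 means. If it is the number randomised and 30% have no usable week-14 value, power is 54%, and 80% holds only for d = 0.68. About 16 of the 26 points lost are then due to drop-out and about 10 to the two-sided test; the whole gap should not be put down to attrition. If 2 × 50 is the analysable number, the 54% does not apply, and the gap is an unstated target of about 72 per group, with two-sided power still about 70%.

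These figures hold under the plan's own t-test approximation. They are not the exact power of the planned ITT/LOCF ANCOVA, because the article quantifies neither the covariate gain nor any dilution from LOCF.

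**What to change.** In the Power section:

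1. Delete the clause claiming that the drop-out estimate entered the sample size calculation.
2. State whether 2 × 50 means subjects randomised or subjects analysed; if analysed, give the number to be randomised.
3. Restate power with its conditions, for example: for the two-sided t-test at an effect size of 0.5, power is about 70% if all 100 subjects contribute week-14 data and the effect is undiluted, and about 54% if 30% are missing at week 14 (35 per group observed).

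This is a change of wording only. It adds no patients and leaves the analysis as planned; the cost is that the stated power becomes less favourable. If the sponsor wishes to claim a gain from the ANCOVA covariates, the assumed baseline-outcome correlation should be stated with it.
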